### Study outcomes and variables

The outcomes of this study are presented in Table 4. The primary efficacy outcome will be the time-averaged proportional change in NT-proBNP concentration from baseline through months 3 and 6. The secondary endpoints included the proportion of patients with an NT-proBNP decrease >20% from baseline through months 3 and 6, composite of all-cause mortality and all-cause hospitalization at 6 months. We will also assess changes in BP, HR, New York Heart Association (NYHA) classification, and quality of life at 6 months. Rate of BP control were under controlled will be compared between the two groups, which is defined as SBP <140 mmHg and diastolic BP <90 mmHg at 6 months. In addition, drug adherence and changes in echocardiographic parameters, including left atrial volume index, left ventricular mass index, E/e', e', pulmonary artery systolic pressure, and GLS will be assessed between the two groups. All adverse reactions and the incidence of the following adverse events of special interest during treatment will be assessed: symptomatic hypotension and bradycardia (investigator-reported).

**Table 4 T4:** Primary and secondary endpoints.

	Endpoints detail
Primary endpoint	Time-averaged proportional change in NT-proBNP concentration from baseline through months 3 and 6
Secondary endpoints	Proportion of patients with NT-proBNP decrease >20% from baseline through months 3 and 6
	Composite of all-cause mortality and all-cause hospitalization at 6 months
	Change in blood pressure and heart rate at 6 months
	Rate of blood pressure control at 6 months
	Change in NYHA classification at 6 months
	Change in quality of life assessed by visual analog scale (0–10)
	Drug adherence at 6 months
	Changes in echocardiographic parameter including LAVI, LVMI, E/e’, e’, pulmonary artery systolic pressure and GLS at 6 months

GLS, global longitudinal strain; LAVI, left atrial volume index; LVMI, left ventricular mass index; NT-proBNP, N-terminal pro B-type natriuretic peptide; NYHA, New York Heart Association.

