Blood sampling tests at the screening visit will be conducted by the laboratories at each participating institute, which are certified by the Korean Association of Quality Assurance for Clinical Laboratory. Measurement of NT-proBNP by an electro-chemiluminescence immunoassay method using cobas® 8,000 (Roche Diagnostics, Mannheim, Germany) will be performed in a central laboratory at randomization and at 6 months (visit 4). Quality of life will be assessed using a visual analog scale ranging from 0 to 10, with 0 being the worst and 10 being best. Drug adherence will be assessed by “pill count” measurements. The patients will bring the remaining tables to each scheduled visit, and trained and certified researchers will count the number of returned drugs and calculate drug adherence as follows:$$\text{Drug adherence }=\frac{\text{number of pills dispensed-number of pills returned}}{\text{number of days between dispensing date and follow-up date}}$$Baseline echocardiographic data collected within 2 months before randomization will be used. All images will be obtained using a standard ultrasound system with 2.5 MHz probes manufactured by GE, Phillips, and Siemens. Standard techniques will be used to obtain the M-mode, two-dimensional, and Doppler measurements. The LV dimensions, LVEF, and other echocardiographic parameters will be obtained according to the guidelines of American Society of Echocardiography and the European Association of Cardiovascular Imaging (32). Echocardiographic parameters at each institution will be archived in the Digital Imaging and Communications in Medicine format. GLS will be evaluated by a central echocardiography laboratory at the Samsung Medical Center, Seoul, Korea. GLS will be assessed using two-dimensional speckle-tracking echocardiography (2D-STE) on index echocardiography (33). The 2D-STE data will be analyzed using TomTec software (Image Arena 4.6, Munich, Germany) for deformation analyses (2-dimensional cardiac performance analysis) (27). For deformation analysis, endocardial borders are traced on the end-systolic frame in three apical views (4-, 2-, and 3-chamber), with end-systole defined by the QRS complex or as the smallest LV volume during the cardiac cycle. The software tracks speckles along the endocardial border and myocardium throughout the cardiac cycle. The peak longitudinal strain is computed automatically, generating regional data from six segments (anterior, anteroseptal, anterolateral, inferior, inferoseptal, and inferolateral) and an average value for each view. The GLS is determined as the average peak longitudinal strain of 18 LV segments from standard apical views. For patients with SR, analyses will be performed on a single cardiac cycle; for patients with AF, the strain values will be calculated as the average of three cardiac cycles. All strain measurements will be performed by strain specialists who are blinded to other data of each patient. All strain analyses will be performed by a single investigator. In our previous study, intra-observer variability in GLS was assessed in 30 randomly selected patients (34). The coefficient of variation has been identified as 5.8% for the GLS, and the intraclass correlation coefficient was 0.95 for GLS [95% confidence interval (CI), 0.91–0.98].

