
### Sample size and statistical analysis

To date, no previous study has evaluated the effects of carvedilol-SR on HFpEF. Due to the absence of prior research and the pioneering nature of our intervention, a sample size calculation was not conducted at this preliminary stage. As this was a pilot study to explore the benefit of carvedilol-SR for HFpEF, we decided to enroll a total of 100 participants (50 in the carvedilol-SR group and 50 in the control group) across the three institutes, considering the duration of the study and the number of participating hospitals.

Categorical variables will be reported as frequencies (percentages), and continuous variables will be expressed as means ± standard deviations or medians with interquartile ranges. Categorical variables will be compared using Pearson's chi-square test or Fisher's exact test, and continuous variables will be compared using Student's *t*-test or the Mann–Whitney *U*-test.

Primary analysis of the proportional change in NT-proBNP concentration from baseline on a logarithmic scale will be performed using an analysis of covariance model with an adjustment for the baseline value. This will be calculated as the average of the geometric means of NT-proBNP at months 3 and 6 divided by the geometric mean of NT-proBNP at baseline in a natural logarithmic scale (i.e., ratio of geometric means) and summarized as the difference between the treatment groups in the ratio of the geometric means. Cumulative clinical-event rates will be calculated according to the Kaplan–Meier method, and the differences in clinical outcomes between the two treatment groups will be assessed using the log-rank test. Hazard ratios and associated 95% CIs will be calculated using a Cox proportional-hazards model. The incidence of adverse events will be calculated as relative risks with associated 95% CIs.

Missing values due to unevaluable samples or early study discontinuation will not be imputed. Patients with missing baseline NT-proBNP and/or missing 3 and 6 months will not be included in the primary analysis. The data will be primarily analyzed using intention-to-treat analysis, including all randomized patients. We will also perform a per-protocol analysis, which include all randomized patients who receive at least one dose of the study drug during the double-blind period and have no major protocol deviations. Safety outcomes will be analyzed in the safety set of patients who received the trial drug at least once.

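### The primary analysis is labelled intention-to-treat in all randomized patients but leaves out those with missing NT-proBNP, under a rule that can be read two ways

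*Protocol article*

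**What the plan says.** Three consecutive sentences under Sample size and statistical analysis in the Protocol article settle who is counted:

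- The first rules out filling in gaps, whatever their cause: "Missing values due to unevaluable samples or early study discontinuation will not be imputed".
- The second then removes patients from the main comparison: "Patients with missing baseline NT-proBNP and/or missing 3 and 6 months will not be included in the primary analysis".
- The third nevertheless names the complete randomized population as the basis: "The data will be primarily analyzed using intention-to-treat analysis, including all randomized patients".

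The endpoint they serve is in Study outcomes and variables: "The primary efficacy outcome will be the time-averaged proportional change in NT-proBNP concentration from baseline through months 3 and 6". The primary analysis "will be performed using an analysis of covariance model with an adjustment for the baseline value". The planned size is 100 patients, 50 per arm, and "a sample size calculation was not conducted at this preliminary stage". No dropout rate is given.

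**The concern.** An ANCOVA with nothing imputed cannot use a patient who lacks a required value. The second sentence accepts this and the third denies it. Whether a patient is excluded is settled after randomization, by events such as death, hospitalization, intolerance or withdrawal. The article itself expects events that could differ by arm: it tracks symptomatic hypotension and bradycardia, and its Discussion cites cohort data linking beta-blockers to more heart failure hospitalization at higher ejection fraction.

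Two things are at stake. A result from a subset would be reported as intention-to-treat in everyone randomized. And the choice between two analyses that respond differently to dropout would stay open until someone resolves the wording, possibly after unblinding.

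**Working it through.** **Step 1. The text.** The article contains no figure to reproduce beyond 50 + 50 = 100. If *m* ≥ 1 patients lack a required value, the primary analysis holds 100 - *m* patients under the exclusion rule and 100 under the intention-to-treat sentence. Nothing elsewhere in the article reconciles the two.

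**Step 2. The two readings.**

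- *Either value missing excludes.* This is a complete-case ANCOVA on the two-visit mean. A patient with month 3 but no month 6 is dropped, and the observed value is lost.
- *Only both missing excludes.* That patient stays, and month 3 alone stands in for the two-visit average.

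Patients are excluded under both readings, so the contradiction in Step 1 does not depend on the choice.

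**Step 3. Size in one assumed scenario, by hand.** All inputs are assumptions: 50 per arm; log-SD 0.9 at each visit (variance 0.81); correlation 0.7 between any two visits; no true effect. The 5 placebo patients (10%) with the largest rise by month 3 are lost before month 6, and 6 active patients (12%) are lost at random.

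- SD of the change to month 3: √(2 × 0.81 × 0.3) = 0.697.
- Covariance of that change with the baseline-adjusted value: month 3, 0.81 × (1 - 0.7 - 0.49 + 0.7) = 0.413; month 6, 0.81 × (0.7 - 0.7 - 0.49 + 0.7) = 0.170.
- Normal density at the 90th percentile: 0.1755.
- *Either* reading: retained placebo patients are shifted by -(0.1755/0.9) × [(0.413 + 0.170)/2]/0.697 = -0.195 × 0.418 = -0.082. Active minus placebo is therefore **+0.082** (ratio 1.085).
- *Both* reading: the placebo mean is shifted by 0.1755 × [(0.413 - 0.170)/2]/0.697 = +0.031. Active minus placebo is **-0.031** (ratio 0.97).
- Standard error with 45 and 44 patients: the residual variance of the two-visit mean is 0.81 × 1.7/2 - 0.49 × 0.81 = 0.2916, so the SE is 0.54 × √(1/45 + 1/44) = 0.114.

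**Step 4. The same scenario simulated, with the dropout mechanism varied.**

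| True log effect | Either missing excludes | Both missing excludes | Likelihood, using month 3 |
|---|---|---|---|
| 0 | +0.049 to +0.082 | -0.019 to -0.030 | 0.000 to -0.001 |
| -0.25 (22% reduction) | -0.170 to -0.202 (16% to 18%) | -0.270 to -0.280 (24%) | -0.250 to -0.251 |

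With an SE of about 0.11, the null bias under the *either* reading is 0.049/0.11 = 0.45 to 0.082/0.11 = 0.75 of an SE. Under the *both* reading it has the opposite sign, and in one such run the type I error was 5.2%.

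**Step 5. When the bias vanishes or reverses.** A second set of assumptions, again with a true ratio of 1.00: log baseline SD 0.8, baseline slope 0.7, residual SD 0.6, residual correlation 0.6. Loss after month 3 depends on the month-3 residual, with logistic slope 0, 1 or 2 per SD. Entries are the complete-case ratio and the type I error at 50 per arm.

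| Loss, placebo/active | Slope 0 | Slope 1 | Slope 2 |
|---|---|---|---|
| 10%/10% | 1.00, 5.3% | 1.00, 5.1% | 1.00, 5.0% |
| 5%/15% | 1.00, 4.8% | 0.96, 7.0% | 0.94, 8.8% |
| 10%/20% | 1.00, 5.5% | 0.96, 6.4% | 0.945, 7.8% |
| 5%/25% | 1.00, 5.3% | 0.925, 10.1% | 0.89, 16.7% |

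Here the bias favours carvedilol-SR, whereas in Steps 3 and 4 it works against it. Over all these cells the *both* reading gave ratios of 0.998 to 1.02, and an analysis using month-3 values under missing-at-random gave 0.998 to 1.002.

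**The case against.** The intention-to-treat sentence can be taken as a general principle for all the data, with the exclusion sentence as its exception for the primary endpoint. That is perhaps what was meant, but the article does not say so, and the phrase about all randomized patients is attached to the main analysis without qualification.

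Other objections carry more weight:

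- The larger bias belongs to one reading only. If both values must be missing, every patient in Steps 3 and 4 stays in.
- The scenario is one-sided by construction. With the same numbers lost but worsening driving loss in both arms, the complete-case null ratio was 0.985. With half of the active loss outcome-related it was 1.03, and with all loss random 1.00.
- The likelihood analysis recovers the truth because dropout was made to depend on an observed month-3 value, which is missing-at-random by design. Table 2 and the laboratory paragraph of Study outcomes and variables list NT-proBNP at randomization and month 6, not at month 3. With a single follow-up value, a mixed model is essentially baseline-adjusted ANCOVA in completers, and the gain disappears.
- A model needing any post-baseline value still leaves out patients who have none.
- This is a pilot with a surrogate endpoint.

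All of these stand as limits on size and severity. None removes the contradiction or the ambiguity.

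**Conclusion.** The contradiction and the ambiguous rule are certain from the text. The bias is conditional: it needs loss that is related to outcome and differs by arm, and it is larger if either missing visit excludes a patient. The illustrative null bias is about +0.05 to +0.08 log units under that reading and -0.02 to -0.03 under the other, in a scenario whose SD, correlation, dropout rates and mechanism are all assumed.

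A reader might infer more, in three ways that the article does not support:

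- *That the primary estimate will be biased, or biased towards one arm.* No dropout rate or mechanism is given, and plausible scenarios point both ways or to no bias.
- *That missing-data sensitivity analyses, or sampling after study drug is stopped, have been left out of the plan.* These may be in a full protocol or analysis plan that is not shown. The exclusion text speaks of leaving the study, and nothing says that sampling ends when the drug is stopped.
- *That the rule would exclude everyone, because month 3 is not scheduled.* This follows only from joining the *either* reading to a separate inconsistency in the sampling schedule, which needs its own correction.

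Severity: should-fix for this pilot trial.

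**What to change.** 1. **Primary model.** Fit a likelihood-based repeated-measures model to log NT-proBNP at months 3 and 6, with treatment-by-visit and baseline-by-visit terms and an unstructured covariance. Include every randomized patient with any post-baseline value. The primary contrast is (δ₃ + δ₆)/2, the mean of the two visit-specific treatment differences, exponentiated to a ratio of geometric means. A constrained longitudinal model, with baseline as a response, does the same and also keeps a patient whose baseline value is missing.
2. **Sensitivity analysis.** Keep the complete-case ANCOVA in this role, and state explicitly that it requires both follow-up values.
3. **Label.** Replace the reference to all randomized patients with an accurate description: patients analysed as randomized who have at least one post-baseline NT-proBNP value. Report how many are left out, by arm and with reasons.
4. **Month 3.** Reconcile Table 2 and the laboratory paragraph with the endpoint so that NT-proBNP is measured at month 3. Without this, item 1 gains almost nothing.

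The cost is a change of wording and modest programming, made before unblinding. The no-imputation sentence can stay. The price is reliance on missing-at-random, which the observed data cannot verify, and patients with no follow-up value still contribute nothing to the contrast.

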Primarily, we will assess the efficacy of carvedilol-SR on the reduction of NT-proBNP in HFpEF compared with a placebo. In addition, we will evaluate the differential effects of carvedilol-SR on primary outcomes according to prespecified variables, including baseline GLS, and NT-proBNP, LVEF. We planned to use the cutoff value of 14% GLS, taking into account a previous study (28), and also planned to use the median cutoff value of the GLS.

All tests will be two-tailed, and a *P*-value <0.05 will be considered statistically significant. Statistical analyses will be performed using R version 4.2.3 (The R Foundation for Statistical Computing, Vienna, Austria).

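### One P<0.05 significance label covers every test in an exploratory pilot, including about 15 secondary comparisons and at least four subgroup analyses

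*Protocol article*

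**What the plan says.** The rule stands at the end of the section Sample size and statistical analysis of the Protocol article: "All tests will be two-tailed, and a *P*-value <0.05 will be considered statistically significant". It does not separate primary, secondary, subgroup and per-protocol analyses. Nothing elsewhere in the article calls the non-primary P-values exploratory or nominal.

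The same section gives the status of the trial: "As this was a pilot study to explore the benefit of carvedilol-SR for HFpEF", with 50 patients per arm and the statement that "a sample size calculation was not conducted at this preliminary stage".

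Table 4, in the section Study outcomes and variables, names one primary endpoint, the "time-averaged proportional change in NT-proBNP concentration from baseline through months 3 and 6". It then lists eight rows of secondary endpoints, for example "Proportion of patients with NT-proBNP decrease >20% from baseline through months 3 and 6", the "composite of all-cause mortality and all-cause hospitalization at 6 months" and "Change in blood pressure and heart rate at 6 months". The statistical section specifies between-group tests for categorical, continuous and time-to-event data, so these rows are meant to be tested and not only described. It also announces a per-protocol analysis beside the intention-to-treat one, and differential-effect analyses by baseline GLS (at 14% and at the median), NT-proBNP and LVEF.

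**The concern.** Read literally, the sentence gives an echocardiographic parameter or a GLS subgroup contrast the same label as the primary endpoint whenever its P-value falls below 0.05. With many such tests and no distinction between them, a chance result is easily reported as a finding.

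The stakes are highest for GLS. The Discussion presents it as a possible way to identify the patients who would benefit from beta-blockers, and it is to be examined at two cut-offs. A chance result at either one, reported as statistically significant, could be taken as a signal for selecting patients for treatment. The stated purpose of the trial is to explore, and the label does not fit that purpose.

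**Working it through.** The article gives no error rate for the family of tests, so there is no figure of its own to reproduce. The check counts the tests and computes the chance of at least one false positive.

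**Step 1: secondary comparisons (Table 4).**

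| Row | Tests |
|---|---|
| NT-proBNP responder | 1 |
| Death or hospitalization composite | 1 |
| Blood pressure and heart rate (systolic, diastolic, heart rate) | 3 |
| Blood pressure control | 1 |
| NYHA class | 1 |
| Quality of life | 1 |
| Drug adherence | 1 |
| Echocardiography (LAVI, LVMI, E/e', e', pulmonary artery pressure, GLS) | 6 |
| **Total** | **15** |

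The total is 14 if blood pressure counts once. It is 17 if the responder endpoint is tested at each month and septal and lateral e' are tested separately.

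**Step 2: subgroup analyses.** GLS at 14%, GLS at the median, NT-proBNP and LVEF make 4, and 15 + 4 = 19. The article's list of subgroup variables is open-ended, so 4 is a minimum. The per-protocol repeats are not counted.

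**Step 3: independent tests, all nulls true.** The chance of at least one P<0.05 among m tests is 1 − 0.95^m.

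- m = 11 (secondary tests without the three blood pressure and heart rate changes and blood pressure control, 15 − 4): 1 − 0.95^11 = 43.1%
- m = 14: 51.2%
- m = 15: 1 − 0.95^15 = 53.7%
- m = 17: 58.2%
- m = 19: 1 − 0.95^19 = 62.3%; expected number of false positives 19 × 0.05 = 0.95

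The case m = 11 matters because the article itself expects this drug class to lower blood pressure and heart rate, so a null hypothesis is implausible for those four tests. Adding the four subgroup analyses to the 11 gives 15 tests again, hence 53.7%.

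**Step 4: correlated tests.** With m test statistics sharing one common correlation ρ, the chance is 1 − E[{Φ((c − √ρ·U)/√(1 − ρ)) − Φ((−c − √ρ·U)/√(1 − ρ))}^m], where U is standard normal and c = 1.96. The article gives no correlations, so ρ is an assumption and a range is shown.

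| m | ρ = 0 | 0.1 | 0.3 | 0.5 | 0.7 |
|---|---|---|---|---|---|
| 11 | 43.1% | 42.3% | 37.5% | 30.4% | 22.3% |
| 15 | 53.7% | 52.5% | 45.7% | 36.1% | 25.6% |
| 19 | 62.3% | 60.8% | 52.5% | 40.9% | 28.3% |

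**Step 5: correlation in blocks.** A simulation with 300,000 draws assumed correlations of 0.5 among the blood pressure and heart rate tests, 0.3 among the echocardiographic tests, 0.1 among the other secondary tests and 0.7 between the two GLS cut-offs. It gave 50.3% for the 15 secondary tests and 58.8% for all 19. For the 11 secondary plus 4 subgroup tests it gave 51.2%.

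**The case against.** The strongest reply is that this is a gap and not an error. The sentence is a routine statement of sidedness and threshold in a condensed article, and handling of multiplicity is commonly left to the statistical analysis plan, which is not shown. That would settle the matter if the article were silent. It is not: it fixes a rule for all tests. If the analysis plan qualifies the rule, the two texts conflict and the published sentence still needs changing. The absence of a multiplicity adjustment is not the complaint, since a pilot does not need one.

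Several other objections stand and limit the point.

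- A reader might infer that the main result is at risk. It is not. There is one primary endpoint with its own ANCOVA, and its 5% error is untouched. The article also ranks its questions, with NT-proBNP first and the subgroups as an addition.
- A reader might infer that a false positive is more likely than not. The documents do not support that. The 54% and 62% need independence and every null true. The 11 secondary tests without blood pressure and heart rate give 43% even when independent, and the 19 tests fall below one half somewhere between ρ = 0.3 and 0.5. Some overlap is certain: E/e' contains e', and the two GLS cut-offs split one variable. The article also names no specific subgroup test, so those four are inferred.
- A reader might blame the missing sample size calculation. Sample size does not enter the formula, and low power does not raise the false-positive rate of a test. It does lower the share of nominally significant results that are real.
- A reader might infer that the pilot is being passed off as confirmatory. The article calls itself a pilot repeatedly and lists the small sample as a limitation.

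**Conclusion.** The point holds as a matter of labelling. The article attaches the words statistically significant to any P<0.05, whether from the primary test, about 15 secondary comparisons (14 to 17 depending on the count) or at least four subgroup analyses, in a trial whose declared aim is exploratory. The chance of at least one false significant result among the non-primary tests is roughly 40% to 60% under plausible counts and moderate correlation. It is lower when fewer tests are counted or correlation is strong: 28% for 19 tests at ρ = 0.7, and 22% for 11. Even that lowest figure is more than four times 5%.

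These figures assume that the counted nulls are true, and the correlations are assumed because the article gives none. The weight is moderate: the primary analysis, the design and the data are unaffected, but what the trial may claim on GLS and the secondary endpoints is affected.

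**What to change.** Replace the sentence with:

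> The primary endpoint (intention-to-treat ANCOVA) is tested at two-sided 0.05. Secondary and subgroup analyses (including both GLS cut-offs) are exploratory, and the per-protocol analysis is supportive; all are reported as estimates with 95% CIs and nominal P-values, without claims of statistical significance.

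If an analysis plan exists, it should carry the same wording. The cost is one sentence and the loss of significance claims on secondary and subgroup results. Keeping such claims would need an adjusted threshold: Bonferroni over 19 tests gives 0.05/19 = 0.0026 per test. The relabelling avoids this, and it leaves endpoints, sample size and data collection unchanged.
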